### Participant recruitment, eligibility and group assignment

Participants are recruited from Fairfield and Pickaway County Children Services. The overall case flow is provided in Fig. 1. Within 7 days of the initial child welfare investigation, parents complete the UNCOPE assessment, a universal screening tool for substance use administered to all parents entering the child welfare system [33]. Parents who score a 3 or higher on the UNCOPE, are considered eligible for EPIC and receive a drug screen. Eligible parents are alternated into EPIC, OhioSTART or treatment as usual (TAU). Ultimately, assignment to EPIC is determined based on caseload, but is typically offered to every third case in Fairfield county and every other case in Pickaway county. Parents who consent to EPIC are connected to peer recovery supporters who mentor parents through the process. Parents are also referred to FTDC with the option to receive MOUD, and lastly when children are placed at home with parents or with kinship caregivers, relational skill building services that include financial assistance for child care, respite and transportation services. EPIC participants receive substance abuse and behavioral health treatment services through local providers including from two partner agencies: Integrated Services for Behavioral Health and Ohio Guidestone.

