### Need for services

Fairfield and Pickaway are adjacent counties in central Ohio. As of the 2010 census, Fairfield County had a population of 146,156, largely composed of Whites (90. 2%), with Blacks representing 6.0% of the population. Southwest of Fairfield is Pickaway County, with a much smaller population of 55,698. Whites make up 94.5% of the population followed by Blacks at 3.4%. Both counties have high rates of opioid-addicted families involved with the child welfare system. The rate of investigations for child maltreatment in Fairfield County is above the state average at 48.09 per 1000 children [14]. Though the rate of child maltreatment investigations is lower in Pickaway County (14.29 per 1000), the number of children in out-of-home care rose over 200% from 23 in 2013 to 73 in 2018 [14, 15]. According to a survey conducted by the Public Children Services Association of Ohio (PCSAO), 79% of families involved in Fairfield County Children’s Services and 67% of families in Pickaway County Children Services have identified substance use problems, both higher than the state-wide average of 50% [16]. In Pickaway County, all the substance-involved families were due to opioid (including heroin) misuse, while 58% of all cases in Fairfield County involved opioids [16]. These rates are over twice the state average of 28% [16]. Thus, while opioid addiction is a particular concern, all types of substance use are affecting children involved in the child welfare system.

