### Evaluation design

To evaluate EPIC, a quasi-experimental design will be employed through a two-stage sampling procedure. This design provides the ability to assess (1) the effects of EPIC on access to services for the families in the two intervention counties, and (2) the independent effects of additional services provided under EPIC that may be over and above interventions provided by Ohio START and treatment as usual (TAU). In the first stage, two comparison counties will be identified for each of the two intervention counties. One comparison county will be part of the Ohio START program while the second will be a county that has no major interventions to address substance use among child welfare families. Counties are matched based on child population size, rate of child protective services referrals, percent of naloxone administrations per adult population, percent white, percent poverty, child welfare tax levy, and to the extent possible, behavioral health service availability. During the second stage, EPIC families (*N* = 250) are matched with substance using families in Ohio START (*N =* 250) and those receiving treatment as usual (*N =* 250).

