### Statistical plan

Baseline descriptive statistics including sociodemographic characteristics, addiction severity and child welfare allegations will be provided for EPIC participants and comparison groups. For continues variables, means and SDs will be provided and for categorical variables, counts and percentages are provided.

Due to the likelihood of censored measures when families are still involved in the child welfare system, survival analysis will be utilized to assess program effects on length of stay in out of home care. Logistic regressions will be used to estimate the relationship between activities and family was reunification, subsequent child maltreatment investigations, and subsequent child maltreatment substantiations. A series of linear regressions will be used to estimate the relationship between our outcome measures and various independent variables (e.g., age, biological sex). Additionally, a paired samples t-test will be conducted to examine the changes in mean scores in child, parent and caregiver well-being outcomes (e.g. ASI or CBCL) between baseline and 6-months follow-up.

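### If Fairfield and Pickaway families not given EPIC serve as comparators, the unequal offer fractions tie group to county; the article leaves the comparator source contradictory and states no county or county-set stratum

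*Protocol article*

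**What the plan says.** The protocol article describes the comparison in two ways.

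- **Participant recruitment, eligibility and group assignment.** Recruitment is from Fairfield and Pickaway. "Eligible parents are alternated into EPIC, OhioSTART or treatment as usual (TAU". The section adds: "Ultimately, assignment to EPIC is determined based on caseload", and EPIC is "typically offered to every third case in Fairfield county and every other case in Pickaway county".
- **Evaluation design.** "In the first stage, two comparison counties will be identified for each of the two intervention counties". Of these, "One comparison county will be part of the Ohio START program while the second will be a county that has no major interventions". Then 250 EPIC families "are matched with substance using families in Ohio START" (250) and with 250 families receiving treatment as usual. The abstract also takes the Ohio START comparators from other counties.

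The Statistical plan uses survival analysis for length of stay in out-of-home care. For the binary outcomes it says: "Logistic regressions will be used to estimate the relationship between activities and family was reunification", and likewise for later investigations and substantiations. Covariates appear only as examples (age, biological sex), for the linear regressions. Neither county nor matched county set is mentioned.

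**The concern.** When the chance of being offered EPIC is about 1/3 in one county and 1/2 in the other, EPIC families and the remaining families in those counties have different county mixes, even if the alternation is followed perfectly. A contrast that ignores county then mixes a county difference into the EPIC effect. This is bias in the estimate, separate from clustering of standard errors.

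The two counties are not alike. Investigation rates are 48.09 and 14.29 per 1000 children. Children in out-of-home care in Pickaway rose from 23 to 73 between 2013 and 2018, while the number in custody in Fairfield stayed steady. Fairfield is described as having little infrastructure for medications for opioid use disorders. If such differences carry over to length of stay, reunification or recidivism, part of them would be read as benefit or harm of EPIC.

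The offer fractions also do not fit a three-way alternation: every other case is 1/2, not 1/3. This adds to the doubt about how comparison families arise.

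**Working it through.** The plan gives no figure for county mix or bias, so there is none to reproduce on this point. The one power figure fully defined in the text, the paired t-test (0.88 at N = 250, effect size 0.2), reproduces at 0.883 two-sided. It is not affected here.

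**Reading A: comparators are the Fairfield and Pickaway families not in EPIC**

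Let p be Pickaway's share of eligible cases. The article does not give p.

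- Pickaway share in EPIC: (p/2) / [(p/2) + (1−p)/3] = 3p/(2+p)
- Pickaway share outside EPIC: (p/2) / [(p/2) + 2(1−p)/3] = 3p/(4−p)
- Leak = difference of the two shares. This is the fraction of any county outcome gap that enters the unstratified contrast.

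A value of p can be built from the Need for services section as investigation rate × population × share of families with substance use, with total population standing in for child population (assumption):

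- Fairfield : Pickaway = (48.09 × 146,156 × 0.79) / (14.29 × 55,698 × 0.67) = 10.4
- p = 1/(1 + 10.4) = 0.088

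Population share alone gives p = 55,698/201,854 = 0.276. The false effect below assumes a 20-point county gap in reunification; the article gives no county outcome figures.

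| p | Pickaway share in EPIC | Outside EPIC | Leak | False effect, 20-point gap |
|---|---|---|---|---|
| 0.088 | 12.6% | 6.7% | 5.9% | 1.2 points |
| 0.20 | 27.3% | 15.8% | 11.5% | 2.3 points |
| 0.276 | 36.4% | 22.2% | 14.1% | 2.8 points |
| 0.40 | 50.0% | 33.3% | 16.7% | 3.3 points |
| 0.50 | 60.0% | 42.9% | 17.1% | 3.4 points |

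The maximum over all p is (√2−1)/(√2+1) = 17.2%.

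Type I error, by a normal two-proportion test with no true effect, 250 v 500 families, and county rates of 40% (Fairfield) and 60% (Pickaway), both assumed:

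- p = 0.088: rates 0.425 v 0.413, SE = √(0.425×0.575/250 + 0.413×0.587/500) = 0.038, z = 0.0117/0.038 = 0.31, rejection about 6%.
- p = 0.40: rates 0.500 v 0.467, SE = 0.039, z = 0.0333/0.039 = 0.86, rejection about 14%.

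Within a county the leak is zero, so a county stratum removes it.

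**Reading B: comparators come from other counties**

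- *Matched within county set.* Each Pickaway EPIC family has comparators from the Pickaway set, and likewise for Fairfield. The offer fractions only decide how many EPIC families each county contributes. The imbalance from the fractions is zero.
- *Matched across pooled sets.* If the comparators' mix followed p (assumption), the gap would be 3p/(2+p) − p: 3.8, 7.3 and 10.0 points at p = 0.088, 0.20 and 0.40. Times the 20-point difference, that is 0.8, 1.5 and 2.0 points, smaller than under Reading A.

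**The case against.** The strongest reply is that the evaluation design, which is the section that defines the comparison, uses other counties, chosen separately for each intervention county. Family matching within those sets is the natural reading, and the unequal fractions then do no harm. This stands: the shares and error rates computed for in-county comparators apply only if the recruitment section's alternation supplies the comparison arms. But matching within sets is not stated, and the recruitment section does describe in-county Ohio START and usual-treatment families.

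A second reply is that a condensed article may leave adjustment terms to an analysis plan that is not shown. That also stands. A reader might infer that the plan rules out stratification; it is only silent. The point rests on the stated allocation rule and the contradiction between two sections, not on the missing term alone.

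Third, the size is modest. At the only p that can be built from the article, rejection is about 6% instead of 5% even with an assumed 20-point gap. The fractions are described as typical and are offers, and consent by county is unknown, so the arm shares are illustrative.

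Two stronger readings are not supported. One is that county differences as a whole are counted as an EPIC effect: at most 17.2% of a gap can enter. The other is that opioid involvement is 100% v 58%. The text reads: "In Pickaway County, all the substance-involved families were due to opioid (including heroin) misuse, while 58% of all cases in Fairfield County involved opioids". The denominators differ. With 67% of Pickaway families substance-involved, a common base gives about 67% v 58%.

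**Conclusion.** The concern holds in conditional form. With in-county comparators and no county term, the offer fractions confound group with county. About 6% (p = 9%) to at most 17% of a Fairfield–Pickaway outcome difference enters the EPIC contrast: 1.2 to 3.4 points for an assumed 20-point gap, with type I error of about 6% at p = 9% and 14% at p = 40%. With out-of-county comparators matched within county set there is no such bias; with matching pooled across sets a smaller one is possible. The article does not settle which case applies. The results rest on the assumed p, the assumed county gap, and consent not altering the offered mix. The paired t-tests compare families with themselves and are untouched.

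**What to change.** 1. Reconcile the recruitment section with the evaluation design on where the Ohio START and usual-treatment families come from.
2. In the evaluation design, state that families are matched within county set (the Fairfield set and the Pickaway set).
3. In the statistical plan, stratify the survival analysis by county set and enter county set as a fixed term in the logistic regressions. If in-county comparators are used, use county itself. Report the stratified estimate as the EPIC effect.

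This takes a few sentences and one degree of freedom; county is known from recruitment. It does not remove confounding between the EPIC counties and their comparison counties: county is nested within group there, so a county-set stratum cannot separate the two.

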**Fig. 1 Fig1:**
[figure not shown]
Enhancing Permanency in Children and Families (EPIC): Case Flow. Parents complete the UNCOPE assessment within 7 days of substantiated report of child abuse or neglect. Parents receive a drug screen if they self-identify on the UNCOPE or a caseworker suspects substance use. Parents who screen positive are eligible for EPIC and are 1) linked to a peer recovery supporter, 2) referred to family treatment drug court, with the option of medications for opioid use disorders, and 3) receive in-home parenting based on the Nurturing Parenting Program. Participants work with assigned caseworkers to determine the most appropriate combination of services

To incentivize participation in FTDC, parents receive a $200 gift card upon completing their substance abuse assessment and an additional $200 retails gift card for every 3 months they remain involved with the court. Parents may consent to one or all three components of EPIC based on the specific needs of each family, however all parents receive intensive case management services, including frequent home visits from caseworkers and peer recovery supporters. All procedures involving human participants were approved by The Ohio State University’s Institutional Review Board (#2018B0001).

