**Methods:**

EPIC is a quasi-experimental study. Under the program**,** child welfare-involved adults who screen positive for substances are matched with a peer recovery supporter. Participants are also incentivized to participate in family treatment drug court, medications for opioid use disorders and home-based parenting supports. Participating adults (*N* = 250) are matched with comparison groups from counties participating in a separate intervention (Ohio START) and to those receiving treatment as usual, resulting in a final sample of 750 adults. Primary outcomes including addiction severity, child trauma symptoms, resilience, and attachment are assessed at baseline and at program completion. Additional outcomes include timely access to treatment services, length of placement in out-of-home care and recidivism into the child welfare system.

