## Methods / design

The overall goals and objectives of the intervention are:
Increase timely access to services among substances abusing parents involved in the child welfare system in Fairfield and Pickaway counties1.1 Develop procedures to coordinate services between the child welfare system, substance abuse and behavioral health providers, and juvenile/family court in a specified single MOU.1. 2 Conduct substance abuse and trauma-exposure screening and assessment within 30 days of entering the child welfare system.1. 3 Reduce the wait time between referral to services and initiation of substance use and behavioral health services.Enhance child safety and improve permanency2.1 Reduce length of stay in out-of-home placement for children in EPIC program compared to substance-affected families not receiving EPIC.2. 2 Increase rates of reunification among families involved in EPIC compared to substance-affected families not receiving EPIC.2. 3 Reduce recidivism for child welfare investigations and re-entries into foster care among parents receiving EPIC compared to substance-affected families not receiving EPIC.2.4 Identify which intervention components implemented via EPIC were more likely to increase positive outcomes for families.Increase child, parent, and caregiver well-being3.1 Decrease substance use/abuse addiction severity among parents and the percentage of parents completing substance abuse treatment who maintained abstinence post-treatment.3. 2 Reduce trauma symptoms experienced by children.3. 3 Increase resilience and attachment in children.3.4 Increase knowledge about trauma-exposure among kinship caregivers.3.5 Improve parenting among kinship caregivers.

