The third and final component of EPIC is *parenting support (Relational Skill Building)* based on the Nurturing Parenting Program (NPP) [20]. NPP focuses on parental expectations of children, empathy toward children’s needs, alternatives to corporal punishment, appropriate parent-child roles, and children’s power and independence [32]. Under EPIC, the program is further enhanced with modules specific to substance use. For example, unexpected challenges related to administering naloxone, a drug that is used to revive individuals who have overdosed on opioids and for kinship caregivers, ways to maintain safe relationships with biological parents. Under EPIC, parents and kinship caregivers may participate in the home-based relational skill building intervention.

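### Peer support appears to go to every EPIC parent, so the design cannot separate it from the EPIC package, yet objective 2.4 and the abstract claim to identify which components work best

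*Protocol article*

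**What the plan says.** **Who receives peer support.** Three places point to every EPIC parent.
- Abstract, Methods: "child welfare-involved adults who screen positive for substances are matched with a peer recovery supporter". The other components are described there as ones that participants are incentivized to join.
- Participant recruitment, eligibility and group assignment: "Parents who consent to EPIC are connected to peer recovery supporters who mentor parents through the process".
- The text after Fig. 1: "all parents receive intensive case management services, including frequent home visits from caseworkers and peer recovery supporters".

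**Wording that points the other way.** The sentence after Fig. 1 opens with "Parents may consent to one or all three components of EPIC based on the specific needs of each family". Study components also lists peer support as the second of three components that participants are incentivized to take up.

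**The other two components.** Family treatment drug court (FTDC) is by referral, with medication for opioid use disorder (MOUD) as an option. Parenting support is offered "when children are placed at home with parents or with kinship caregivers, relational skill building services", and the component description says that "parents and kinship caregivers may participate in the home-based relational skill building intervention". The Fig. 1 caption adds: "Participants work with assigned caseworkers to determine the most appropriate combination of services".

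**What is promised.** Objective 2.4 (Methods / design) is to "Identify which intervention components implemented via EPIC were more likely to increase positive outcomes for families". The discussion paragraph of the abstract goes further: it says that using three strategies lets the study find which of them work best at lowering addiction severity. Neither statement makes an exception for peer support.

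**The concern.** To say which of several components works, some families must have a component and others not, or its amount must vary, and that variation must be separable from everything else the family receives. If every EPIC family has a peer supporter, the first kind of variation is absent within EPIC. The contrasts in Evaluation design do not supply it, because they compare the EPIC package with Ohio START and with TAU.

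A reader deciding which parts of EPIC to fund or sustain could take a ranking of components as covering peer support when no such contrast exists. The rankings of the other two would also mislead, because their uptake follows family need, child placement and willingness to engage, each of which may itself predict the outcome.

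**Working it through.** **1. Is delivery universal?** The sentence after Fig. 1 first allows a choice among components, then turns with a *however* to what all parents receive, which includes visits from peer recovery supporters. The abstract and the recruitment section agree with that second half. The Fig. 1 caption is not used for this step, because it describes in-home parenting in equally universal terms. The best reading is planned delivery to all 250 EPIC families (sample size from Evaluation design). The article reports no uptake figure.

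**2. Within EPIC.** Take the model

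outcome = b0 + b1·peer + b2·FTDC + b3·parenting.

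If peer = 1 for all 250 families, its column equals the intercept column. With FTDC and parenting varying (simulated values), the matrix has rank 3 of 4: only b0 + b1 is estimable, not b1. If a visit count that varies replaces the yes/no term, the rank is 4 of 4.

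**3. Across the three groups (N = 750).** The columns are intercept, EPIC, START, peer, FTDC and parenting. Receipt of peer support in the comparison groups is not given, so three cases are assumed:
- Peer support only in EPIC: the peer column equals the EPIC column; rank 5 of 6.
- Universal in EPIC and in START: the peer column equals EPIC + START; rank 5 of 6.
- Received by half of START: rank 6 of 6, but the contrast then comes from START families and no EPIC family contributes to it.

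**4. Which outcomes are affected?** Objective 2.4 sits under the safety and permanency goal. Its outcomes come from state administrative data, and the survival and logistic models are sized at N = 750, so step 3 is the relevant one. For addiction severity, the outcome named in the abstract's discussion, Data sources describes EPIC family surveys, and Power analysis sizes the linear regressions and paired tests at N = 250. That suggests, without proving, an EPIC-only analysis, to which step 2 applies.

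**5. If some EPIC families go without (illustration only).** The plan gives no power for a component contrast. Its nearest figure is 0.88 for the paired t-test with N = 250 and effect 0.2. With noncentrality 0.2 × √250 = 3.16, 249 degrees of freedom and two-sided alpha 0.05, the power is 0.883, so the figure reproduces.

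Now let k of 250 families lack peer support, with k assumed. The standard error in SD units is √(1/k + 1/(250 − k)). Power is from a two-sample t-test with 248 degrees of freedom, two-sided alpha 0.05 and no covariate adjustment. The plan's 0.2 is read as a standardised difference.

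| k without | SE | 0.2/SE | Power at 0.2 SD | Detectable at 80% power |
|---|---|---|---|---|
| 5 (2%) | 0.452 | 0.443 | 7% | 1.27 SD |
| 12 (5%) | 0.296 | 0.676 | 10% | 0.83 SD |
| 25 (10%) | 0.211 | 0.949 | 16% | 0.59 SD |
| 125 (50%) | 0.126 | 1.581 | 35% | 0.36 SD |

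The last row is a reference for an elective component taken up by half. A small group that goes without peer support would also be unplanned and self-selected.

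**The case against.** The strongest reply is that the article never commits to a yes/no contrast. Objective 2.4 speaks only of components more likely to help, and the Statistical plan relates outcomes to activities without saying how they are coded. Peer supporters log visits in the Needs Portal, so a dose analysis is open, and the coding of exposure may be left to a fuller document. This stands in part. A reader might infer that the plan specified a received/not-received test that fails, or that nothing about peer support can be learned; the document supports neither. What remains is that no coding creates unexposed families, and that number of visits answers a different question and may follow need and engagement.

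Second, universal delivery is an inference. Being able to choose one component, taken literally, allows a choice without peer support, and being linked to a supporter is not the same as receiving the component. This also stands in part: 250 of 250 is the better reading, not a stated fact. If peer support is truly elective, the sentence after Fig. 1 conflicts with itself and still needs correcting.

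Third, the N = 750 analyses could identify peer support if its receipt varied within Ohio START or TAU. That is correct, but the article does not report such variation, and the information would come from outside EPIC.

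Fourth, the abstract's sentence speaks of an opportunity, and the study is openly quasi-experimental. Both are fair. Even so, the sentence names finding the most effective strategies as what the design offers, and for peer support it does not offer that.

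**Conclusion.** The point holds in a limited form. On the best reading of the article, the presence or absence of peer support cannot be separated from the EPIC package, either within EPIC or through the whole-program contrasts, unless receipt varies within a comparison arm. Objective 2.4, and more clearly the abstract's claim about addiction severity, go beyond the design for this component.

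The size is structural: the coefficient is not estimable under planned delivery, whatever the sample size. The shortfall powers of 7% to 16% rest on assumed values of k and are illustrative only.

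A reader might conclude that objective 2.4 is void. That does not follow. FTDC with MOUD and parenting support vary within EPIC and can be related to outcomes. But they vary by need, placement and choice, so these results are associations and cannot by themselves rank the strategies. The program-level comparisons on placement, reunification and recidivism are untouched. The change is worth making because it alters what the study may conclude, but it does not threaten the main evaluation.

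**What to change.** - In Study components and in the text after Fig. 1, state that peer support is core to every EPIC package and that FTDC (with optional MOUD) and parenting support are elective.
- Limit received/not-received comparisons under objective 2.4 to the elective components.
- Assess peer support through the number or intensity of visits logged in the Needs Portal.
- Reword objective 2.4 and the abstract's discussion so that all component-level results, visit intensity included, are exploratory associations open to confounding by need and engagement, and do not rank the strategies.

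The cost is wording. Visit logging is already provided for (Collaboration, coordination and cross-training), and no new sample or procedure is required. The downside is a narrower claim: EPIC could not report a received/not-received effect for peer support.
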